Treatment Assignment	Individual randomization, stratified on disease status (MS, IBD, CIRD or none of these).	To emulate randomization we adjust for multiple confounders using a combination of matching and g-computation.
Start and end of trial	(1) Herpes zoster vaccine effectiveness trial: 01.12.2018–31.12.2021^a^ (2) Influenza vaccine effectiveness trials:*^b^* (a) 01.09.2015–31.05.2016 (b) 01.09.2016–31.05.2017 (c) 01.09.2017–31.05.2018 (d) 01.09.2018–31.05.2019	
Start and end of follow-up	Start of follow-up: time of assignment to treatment strategy. End of follow-up: The earliest of death, loss-to-follow-up or administrative end-of-follow-up (end of the respective study).	
Outcomes	(1) Herpes zoster vaccine effectiveness: medically attended Herpes zoster infection (2) Influenza vaccine effectiveness: (a) medically attended influenza infection (b) severe medically attended influenza infection	
Causal contrast	(1) The ratio between the vaccine effectiveness (1 - the relative risk to develop the outcome at time *t* given the treatment) in the diseased group (individual has either MS, IBD or CIRD) and the non-diseased group (2) The vaccine effectiveness for each of the three disease groups (MS, IBD, CIRD), stratified by the categorized severity of received medication in regards to immunosuppressive effect. Both contrasts will be estimated as *intention-to-treat* and *per-protocol* effects. The target estimand is the average causal effect on the treated (ATT).	
Statistical analysis	Computing formal contrasts of simple Kaplan-Meier estimates.	Time-dependent 1:1 matching by days without replacement. Controls will be matched exactly by age in years, biological sex, place of residence, and disease status. The matched sample will be analyzed using a Cox model with additional adjustment for further confounders. G-computation based on this Cox model and a non-parametric estimate of the baseline hazard will be used to estimate the target estimand. Both *intention-to-treat* and *per-protocol* effects will be estimated by different censoring schemes as described in Section 2.6.3.
Sensitivity analysis	None.	The entire analysis will be repeated using *medically attended urinary tract infection* as a negative control outcome to assess the robustness of the confounder adjustment employed.

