The target trial for the influenza vaccine is very similar, but differs slightly due to the seasonality of the disease. Influenza viruses are constantly mutating, necessitating yearly changes of the influenza vaccines. It is therefore recommended to estimate influenza vaccine effectiveness on a seasonal basis instead (30). The target trial is therefore also defined on a seasonal basis, meaning that there is one target trial per influenza season that should be emulated. Recruitment would start each year on the first of September. People may then be recruited and followed up until the end of May of the next year (31.05.).

Both target trials are pragmatic, in the sense that no placebo control is used. We choose to formulate them this way because it is generally impossible to emulate placebo-controlled randomized controlled trials using only observational data (27). We further assume perfect adherence, so that every individual randomized to the treatment group actually receives the respective vaccination strategy and every individual in the control group does not. Our main interest is therefore in the *per-protocol* effect, although we will also estimate *intention-to-treat* effects in a sensitivity analysis, as described in detail in Section 2.6.3. Because we compare the vaccine effectiveness of patients with autoimmune diseases and other patients, but are unable to randomize the disease status itself, we are interested mainly in the *effect modification* of the disease status on the vaccine effectiveness (31). The result is a comparison of two population-based total causal treatment effects (32).

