### 2.4 Study period

Although information between 2013 and 2021 is available, we will not use this entire duration as a study period for all of the target trial emulations. First, as described in Section 2.2, there will be one trial emulation per influenza season, with only the time during the respective season being included. Secondly, the first influenza vaccine effectiveness trial emulation will start with the influenza season of 2015/2016 and not with influenza season of 2013/2014, because we need two years of previous follow-up to determine eligibility of the individual and to measure the relevant confounders. Finally, although information for a fifth trial emulation in the influenza season of 2019/2020 would be available, we will not perform this analysis. The reason for this decision is that the COVID-19 pandemic started during this season and largely overshadowed the influenza season of this year. The likely large amounts of underreporting of influenza infections during the COVID-19 pandemic, combined with the actual effects of the pandemic and the measures taken to combat it (33), make a target trial emulation infeasible. Similarly, the target trial for the herpes zoster vaccine effectiveness analysis only starts on the 01.12.2018, because the inactivated herpes zoster vaccine was not available in Germany and not recommended by the STIKO (in German: “Ständige Impfkommission”) before this date (29).

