#### 2.5.3 Outcomes

Different outcomes will be used for each of the considered vaccine effectiveness trials. For the emulation of the proposed target trials, the date on which the respective outcomes occurred is required. Our aim is therefore to identify this date of occurrence given the available insurance claims data. In the German system, ICD-10 codes that were used in the inpatient setting are directly associated with an exact date. Outpatient ICD-10 diagnosis, however, are only associated with a time interval which may be up to 91 days (one quarter) long, depending on the patient. In some cases, the corresponding date of the diagnosis must therefore be identified using associated treatments or doctors certificates on the incapacity to work, for which exact dates are available. The concrete strategy used to identify the dates for outpatient diagnosis of each defined outcome and associated sensitivity analyses are described in the online supplement.

The outcome for the herpes zoster vaccine effectiveness analysis is a *medically attended herpes zoster infection*. This outcome will be identified from the available data through the use of ICD-10 code **B02** (inpatient or outpatient diagnosis), in conjunction with a prescription for an antiviral drug (acyclovir, valacyclovir, famciclovir, or brivudin). This is similar to the definition proposed by Zerbo et al. (44), which was estimated to have a positive predictive value of 96.7% by the same authors. Other studies additionally employed information about positive laboratory tests (45), which is not possible in this study due to a lack of available data.

For the influenza vaccine trials we will use *medically attended influenza* as the primary outcome, as recommenced in the literature (30, 46). We define a medically attended influenza as an influenza infection that results in any type of formal contact between the patient and a health care professional. In particular, we define a medically attended influenza infection as having occurred when either one of the ICD-Codes **J09**, **J10**, or **J11** has been used as a secured outpatient diagnosis or in an inpatient main or secondary diagnosis. The medically attended influenza is considered to be *severe* if it is associated with a hospital admission due to pneumonia or death. We will use the severe medically attended influenza as a secondary outcome.

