For most of the relevant confounders identified through the DAG, one or multiple indicators can be extracted from the available BARMER data, as described above. However, this is not the case for all confounders. For example, we were unable to identify valid indicators for the *Cautiousness* of an individual. We are thus unable to adjust for all confounders, potentially resulting in a violation of the *conditional exchangeability* assumption (e.g., that the groups are exchangeable given the observed confounders) (32). Although social contact behavior is a crucial factor in infection transmission and thus an important predictor for the outcomes in our study, its role as a predictor for vaccination decisions is less clear. A study by Ibuka et al. (54) indicates that people with less cautious contact behavior only have a slightly higher chance of getting vaccinated. We therefore expect the bias introduced by this unmeasured confounder to not be substantial.

An additional issue in the adjustment is that not all considered confounders are measured perfectly. In particular, the influenza and herpes zoster immunity at baseline will likely be underestimated, because not all individuals who experienced an infection visited a medical professional because of it. Hence, not all infections are included in the data, resulting in some individuals appearing as not having been infected, despite having been infected. Furthermore, because we only have access to the data between 2013 and 2021, we will likely underestimate the true extent of the existing herpes zoster immunity as well, because most chickenpox infections happen during childhood and we did not measure childhood vaccinations. These measurement errors may result in additional residual confounding (43). Sensitivity analysis will be performed to further quantify this potential source of bias, as described in Section 2.6.6.

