Controls will be matched without replacement, meaning that individual *i* who was used as a control at one point in time *t* cannot serve as control more than once at the same point in time and can also not be used as control again at later points in time. However, people who have been used as controls will still be included in the trial later, if they get vaccinated. They will then be included in the treatment group, again with the vaccination date corresponding to the trial inclusion date. Information about the different defined outcomes are extracted from the BARMER data for each individual. This matching procedure results in datasets that are similar to what we would obtain if we actually had performed the respective target trials. The main advantage of this method is that it directly matches patients by inclusion-date, giving us a clearly defined “time zero” (27). Because controls are choosen to be similar to vaccinated individuals, this matching methods targets the *average treatment effect on the treated* (ATT) (56).

If no suitable control can be identified for a vaccinated individual at the time of vaccination, the individual is not included in the analysis. Because of the large amount of data, the long follow-up time and the fact that only a relatively small proportion of individuals gets vaccinated, we believe that only a small proportion of individuals will be excluded. If the proportion of vaccinated individuals with no matched controls exceeds 10%, we will adjust the choice of matching variables to lower this proportion. This will be done by either widening the age groups or not matching by sex. In theory, methods other than exact matching, such as generalized full matching (59) would offer a viable alternative in such cases. It would also allow matching on more confounders, which would be preferable. We unfortunately cannot use such methods, due to the high computational complexity of our approach and the limited available technical infrastructure.

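### The influenza analysis pools coded events from before and during virus circulation, and its one negative control does not share the contact-behaviour cause that the plan cannot adjust for

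*Protocol article*

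**What the plan says.** All places are in the protocol article.

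- **Window.** Table 1 lists the influenza trials as "a) 01.09.2015–31.05.2016 (b) 01.09.2016–31.05.2017 (c) 01.09.2017–31.05.2018 (d) 01.09.2018–31.05.2019". Section 2.2 adds "Recruitment would start each year on the first of September", and Section 2.4 says "there will be one trial emulation per influenza season, with only the time during the respective season being included". Season here means this fixed window. No dates of virus circulation are given.
- **Follow-up.** Table 1: "Start of follow-up: time of assignment to treatment strategy". Section 2.6.1 repeats enrolment daily until the trial ends, and says "The main advantage of this method is that it directly matches patients by inclusion-date".
- **Outcome.** Section 2.5.3 counts an event when J09, J10 or J11 "has been used as a secured outpatient diagnosis or in an inpatient main or secondary diagnosis". No laboratory or circulation condition is stated. Outpatient diagnoses are "only associated with a time interval which may be up to 91 days (one quarter) long". The rules for assigning dates are in an online supplement that is not shown.
- **Effect measure.** Section 2.6.2 fits a Cox model with a vaccine-by-disease interaction and derives VE(t) = 1 − RR(t).
- **Residual confounding.** Section 2.5.4 finds no valid indicator for cautiousness, calls social contact central to transmission, and concludes "We are thus unable to adjust for all confounders". It expects the bias to be small on the strength of one cited study, and refers to Section 2.6.6 for sensitivity analysis. That section names one negative control outcome, urinary tract infection, for all analyses. It asks that such an outcome ideally share the causes of the outcome of interest.

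**The concern.** There are two linked weaknesses.

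**Dilution.** Influenza is seasonal, so part of a window that opens on 1 September probably precedes circulation. A code recorded then is probably another illness, which the vaccine cannot prevent. Such events pull the pooled VE towards zero. If their share differs between diseased and non-diseased people, they also move the VE ratio, which is the main contrast. VE(t) does not expose this, because t counts days since inclusion and inclusion is spread over calendar days. Matching on inclusion date balances calendar time between the arms but does not separate the periods.

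**A gap in the bias check.** The confounder that the plan names and cannot measure is contact behaviour. Urinary tract infection is not passed on by social contact, so a null result there cannot rule out bias by that route. It also does not test how influenza codes are used. Events coded as influenza before circulation share the codes and the coding practice. As far as they are other respiratory infections, they share contact transmission too. The plan holds these data and does not use them in this way.

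**Working it through.** The article gives no event count, event rate, power or circulation date on this point, so there is no figure of its own to reproduce.

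**Inputs**
- From Table 1: windows of 274, 273, 273 and 273 days, counted inclusively.
- Assumed: true VE = 0.40; s, the share of control-arm coded events before circulation; c, the rate ratio due to residual confounding, taken as equal in both periods; vaccine effect zero before circulation.

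**1. Pooled VE.** Pooled VE = 1 − c × [s + (1 − s)(1 − VE)]. Without confounding (c = 1):

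| s | Pooled VE |
|---|---|
| 0 | 0.40 |
| 0.05 | 0.38 |
| 0.10 | 1 − (0.10 + 0.90 × 0.60) = 0.36 |
| 0.20 | 0.32 |
| 0.30 | 0.28 |

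With s = 0 there is no dilution. Virus-free weeks with no coded events do no harm.

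**2. Adding confounding.** At s = 0.10, c = 0.8, 0.9, 1.1 and 1.2 give pooled VE of 0.488, 0.424, 0.296 and 0.232. In reverse, a pooled VE of 0.40 fits a true VE of 0.278 (c = 0.8), 0.370 (0.9), 0.444 (1.0), 0.505 (1.1) or 0.556 (1.2).

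Restricting to circulation removes the dilution but not the confounding: with c = 0.9, circulation-only VE is 1 − 0.9 × 0.60 = 0.46 against a true 0.40. Under these assumptions the pre-circulation estimate would return RR = c.

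**3. The VE ratio.** Equal true VE in both groups, so the true ratio is 1:
- s = 0.10, c = 0.9 in both groups: 0.424 / 0.424 = 1.00.
- s = 0.10, c = 1.0 in the diseased and 0.9 in the non-diseased: 0.360 / 0.424 = 0.85.
- s = 0.10, c = 1.1 and 0.9: 0.296 / 0.424 = 0.70.
- No confounding, s = 0.20 in the diseased and 0.10 in the non-diseased: 0.32 / 0.36 = 0.89.

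**4. What a pre-circulation check could detect.** With d events in both arms together and 1:1 matching, the 95% limits are RR ×/÷ exp(1.96 × √(4/d)). For an observed RR of 0.85:

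| d | Factor | Upper limit |
|---|---|---|
| 500 | 1.19 | 1.01 |
| 1,000 | 1.13 | 0.96 |
| 2,000 | 1.09 | 0.93 |

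For 80% power at two-sided 5%, the events needed are 4 × (1.96 + 0.84)² / (ln RR)²: about 1,190 at RR 0.85, and 631 and 2,829 at RR 0.8 and 0.9. With two controls per case the last two become 710 and 3,182.

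**The case against.** A reader might infer that the plan leaves residual confounding and vaccine effect impossible to tell apart. The article does not support that. Section 2.6.6 plans a negative control outcome for exactly this purpose, in all analyses, and Sections 2.5.4, 2.6.5 and 3 disclose the remaining risk. What is missing is a check that covers contact behaviour and influenza coding.

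Other objections, and what stands of them:

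- **The 1 September opening is not itself a fault.** Follow-up has to start at vaccination to keep a valid time zero, and controls enter on the same day. Harm by dilution needs coded events before circulation, and the article gives no count. This stands.
- **The proposed check is indirect too.** If the early codes are not influenza, they are another illness under the same code. This stands, but it is a different indirect check from urinary tract infection, closer in coding and possibly in transmission.
- **VE is already time-dependent, and time-dependent hazard ratios are a fallback.** True, but on time since inclusion, so calendar periods stay mixed.
- **Dating is blurred.** Where outpatient events are known only to the quarter, epidemic events misdated into the earlier period would give a positive pre-circulation VE from real protection. This stands and limits both the cut and its reading.
- **A positive pre-circulation VE might be taken to show how much of the seasonal VE is bias.** That holds only if confounding is equal in both periods, which nothing in the article establishes.
- **A few hundred early events might be thought enough.** At 500 events the interval around RR 0.85 still includes 1.

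**Conclusion.** The point holds as a worthwhile, inexpensive improvement. It is not an error or an internal contradiction in the article.

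The fixed window, the code-based outcome and the absence of any calendar split are plain from the text. So is the mismatch between the confounder named as unmeasured in Section 2.5.4 and the negative control chosen in Section 2.6.6.

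The size is illustrative. Under the assumed VE of 0.40, an early share of 10% to 20% lowers pooled VE to 0.36 to 0.32, and there is no dilution if nothing is coded early. The VE ratio moves only if the early share or the confounding differs between groups: to 0.89, 0.85 or 0.70 in the examples. VE, the shares, the confounding ratios and the event counts are all assumptions, as is the premise that some of the window precedes circulation. Without counts, feasibility cannot be judged, except that pooling over seasons will probably be needed.

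**What to change.** 1. Before analysis, fix each season's circulation period from national surveillance by a stated rule, and say how follow-up after its end is handled.
2. Because of the dating limits, place the cut at a quarter boundary where surveillance allows. Otherwise, base the split on events with an exact date only.
3. Keep time zero and the matching as planned. Split follow-up at the cut and fit the planned model with separate vaccine effects before and during circulation, by disease group.
4. Report circulation-period VE beside the whole-window VE.
5. Report pre-circulation VE and its diseased versus non-diseased contrast, pooled over the four seasons, as a second negative control beside the urinary tract infection result.
6. State the reading rule in advance. A clearly non-null pre-circulation VE is a warning of residual bias, not an estimate of its size during the epidemic, because confounding may differ between periods and misdated epidemic events can mimic it. A wide interval around zero is not reassurance.

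Cost: a split in models already planned and one more table, with no new patient data but with published surveillance dates needed. Precision will be low in MS and IBD, and an exact-date restriction would reduce it further.

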### 2.5 Measures

#### 2.5.1 Disease definitions

We will consider three main types of autoimmune disease groups: MS, CIRD, and IBD. To determine whether an individual has developed one or multiple of the diseases contained in each group at certain points in time using the BARMER data, we developed new algorithms based on previous research. For MS all existing subtypes of the disease are considered. Our algorithm to identify MS is loosely based on the algorithm developed by Culpepper et al. (34). We further define an individual to have CIRD only when that individual either has *rheumatoid arthritis, axial spondyloarthritis* or *systemic lupus erythematosus*. Those three diseases are each identified using different algorithms, based on previous work (35–37). Similarly, we define IBD to be present if the individual has *Crohn's disease* or *colitis ulcerosa*, which are also identified separately using algorithms based on previous research (38, 39). The exact definitions used for each disease and sub-disease are given in the online supplement of this article.

Through the course of the VAC-MAC project, these definitions have already been applied to the BARMER data. We were able to identify approximately 50,000 patients with MS, 300,000 patients with CIRD and 80,000 patients with IBD between the 01.01.2013 and the 31.12.2021. Additionally, approximately 9,000 of these patients had more than one of the three considered disease categories. Although this constitutes a “look into the data” before this study protocol was published, this procedure is in accordance with recommendations by Wang and Schneeweiss (40), who state that performing data checks before study registration actually increase the validity of the study.

#### 2.5.2 Treatments

The “treatments” in this study are the two different types of vaccines of interest. We will not differentiate between different subtypes of vaccines in the influenza vaccine effectiveness trials. Any vaccine against influenza will be considered an “influenza vaccine”, regardless of its' underlying mechanism and irrespective of which company created the vaccine. In the herpes zoster trial we will only consider the inactivated recombinant zoster vaccine (Shringrix^®^) (41). In Germany, vaccinations are usually provided by physicians in primary care. Physicians receive a reimbursement for each vaccination from the statutory health insurance of the individual being vaccinated. To this end, a standardized reimbursement code [German: Gebührenordnungsposition (GOP)] is used and transferred to the insurance as part of a reimbursement claim. We will use these codes to identify vaccinations in our study population, using both codes applying uniformly for all regions in Germany and codes only used for specific regions and time periods. The reimbursement codes used are listed in the online supplement.

There is, however, one special case that needs to be mentioned. Whenever individuals get vaccinated through a company physician (in German: Betriebsärzte), the reimbursement code is not transferred to the insurance company of the individual. The reimbursement is instead taken care of by the companies themselves. Additionally, a few pharmacies and hospitals also vaccinate individuals without sending reimbursement codes to the insurance company (42). Because these vaccinations never show up in the individuals data of the health insurance, the vaccination status of these individuals will be misclassified in the analysis. We expect this issue to have a minor impact, because the majority of vaccinations are performed by primary care physicians in Germany. There is currently no official data available to quantify the proportion of vaccinations performed in these different settings. Due to the complex nature of the proposed analysis strategy, as described in Section 2.6, it is also not possible to apply standard methods of quantitative bias analysis to quantify the effects of this potential bias (43). To still get a rough estimate of the potential impact of this misclassification, we will repeat the main analysis after removing 10% of all vaccination dates from the available data in a sensitivity analysis.

